##### Glucose tolerance.

To evaluate glucose tolerance, fasting capillary blood glucose and venous insulin are measured on the day before or the day of study inclusion as well as on day 5 of therapy. Homeostasis model assessment of insulin resistance (HOMA-IR) is computed with the following formula: HOMA-IR = fasting plasma glucose (FPG, mg/dL) × immunoreactive insulin (IRI, μIU/mL)/405 [34]. Serum samples from baseline and visit 6 are analyzed in the central laboratory in Halle (Saale), and blood glucose is measured locally.

For the time schedule of assessments and visits, see Table 2.

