### Participant timeline {13}

For the time schedule of enrolment, interventions, assessments, and visits for participants, see Table 2.

**Table 2 Tab2:** Time schedule of enrolment, interventions, assessments, and visits for participants

	BL^a^			Therapy			Th. end	FU 1^b^	FU 2^b^
Visit	1	2	3	4	5	6	7	8	9
Day	−6 to 1	1	2	3	4	5	10–13	30 ± 4	180 ± 14
*Demographic data*	X	-	-	-	-	-	-	-	-
*Informed consent*	X	-	-	-	-	-	-	-	-
*Inclusion and exclusion criteria, medical history*	X	-	-	-	-	-	-	-	-
*Physical examination*^1^	X	-	-	-	-	-	-	-	-
*Laboratory assessments*^2^									
Complete blood count	X	-	-	-	-	-	-	-	-
Clinical chemistry tests	X	-	-	-	-	-	-	-	-
Pregnancy test	X	-	-	-	-	-	-	-	-
Blood sample (fasting) for central laboratory^3^	X^3^	-	-	-	-	X^3^	-	-	-
Shipment of samples to central laboratory	-	-	-	-	-	X	-	-	-
POCT-glucose (before medication)	X^c^	X^c^	X	X	X	X	X	X	X
*Audiological assessments*^4^									
Pure tone audiometry	X^c^	X^c^	-	X^5^	-	X^5^	X	X	X
Impedance audiometry	X	-	-	-	-	-	-	X	X
Speech audiometry	X^c^	X^c^	-	X^5^	-	X^5^	X	X	X
*Otoneurological assessment*^6^	X		-	-	-	-	-	-	-
*Blood pressure, pulse*	X^c^	X^c^	X	X	X	X	X	X	X
*Long-term blood pressure*	-	-	-	-	-	X^7^	-	-	-
*Study medication*									
Documentation of concurrent medication	X	X	X	X	X	X	X	X	X
Application of study medication i.v.	-	X	X	X	X	X	-	-	-
Dispensing of p.o. medication and instruction	-	X	-	-	-	X	-	-	-
*Documentation of adverse events (AEs)*	-	X	X	X	X	X	X	X	-
*Documentation of quality of life (QOL)*	X^c^	-	-	-	-	-	-	X	X
*Documentation of tinnitus*	X^c^	-	-	-	-	-	-	X	X
*Indication for hearing aid/cochlear implant*	-	-	-	-	-	-	-	X	X
*MRI*	X								
*CRF-documentation/drug accountability*	X	X	X	X	X	X	X	X	X

*POCT* point-of-care testing, *Th. end* end of drug therapy

^a^
*BL* baseline

^b^
*FU* follow-up, FU 1: primary endpoint

^c^ Assessments at visits 1 & 2 can be made on the same day, e.g., the patient may receive the first study medication on the day of enrolment. Assessment of baseline blood glucose, pure tone and speech audiometry, blood pressure, pulse, quality of life and tinnitus should not take place more than 1 day before the first study medication

^1^ Includes: physical examination of all organ systems, weight, size, ENT examination, body temperature

^2^ Includes: complete blood count, clinical chemistry tests (ALAT, ASAT, GGT, ALP, creatinine, sodium, potassium, calcium, CRP), pregnancy test (hCG)

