^3^ Central laboratory evaluations: measurement of HbA1c (baseline only), insulin, HOMA-IR (baseline and V6), fasting if possible, blood sample must be taken before medication; if V6 Saturday or Sunday or holiday: blood sample may be taken at last or next working day

^4^ Pure tone audiogram 250–8000 Hz, bone and air conduction; impedance audiometry, speech (monosyllables at 65 and 80 dB SPL with Freiburger speech test)

^5^ If visit on Saturday, Sunday or holiday these assessments may be omitted

^6^ Includes: spontaneous nystagmus, caloric or head impulse test, Romberg test; may be done at V1 or V2, at V2 also after medication possible

^7^ Day 5 ± 2 days

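### The HOMA-IR instructions disagree on fasting, specimen and timing, and insulin drawn after day 5 has no scheduled same-day glucose

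*Protocol article*

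**What the plan says.** The abstract lists altered glucose tolerance among the secondary endpoints. The Secondary outcomes section explains that HOMA-IR was chosen because it detects altered glucose metabolism more sensitively than glucose alone.

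Under Assessments of systemic safety aspects, the Glucose tolerance section states that "fasting capillary blood glucose and venous insulin are measured" at two points: first at inclusion or one day earlier, then on the fifth treatment day. It then computes HOMA-IR as fasting plasma glucose (mg/dL) times insulin (μIU/mL) divided by 405, and adds: "Serum samples from baseline and visit 6 are analyzed in the central laboratory in Halle (Saale), and blood glucose is measured locally".

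Table 2 and its footnotes say something different:

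- The central-laboratory sample row is labelled fasting, but its footnote 3 reads "fasting if possible, blood sample must be taken before medication".
- For a visit 6 on a Saturday, Sunday or holiday, the same footnote says the "blood sample may be taken at last or next working day". It lists insulin and HOMA-IR as central evaluations and names no central glucose assay.
- The point-of-care glucose row says only that the reading precedes medication. It is scheduled at every visit, has no fasting label and carries no weekend allowance.
- Footnote c says that baseline glucose "should not take place more than 1 day before the first study medication". The central-sample row does not carry footnote c, and visit 1 spans day −6 to day 1.

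**The concern.** HOMA-IR is a product of two concentrations and is defined for a single fasting moment. If the two factors come from different days, or from a patient who has eaten, the product no longer measures what the formula describes. The article fixes the day and the fasting state in one place and relaxes both in another, without saying which glucose value goes with an insulin sample that has moved.

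The timing point matters most. The high-dose courses stop after day 5 without tapering, whereas the control arm goes on to five tapering doses. An insulin sample drawn after day 5 can therefore reflect different recent exposure in different arms. Randomisation and blinding do not remove that difference, because it belongs to the regimens themselves. The Background presents the comparison of glucose effects between dose schedules as an important topic, and the parallel 24-hour blood pressure measure has explicit validity criteria. HOMA-IR has none.

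**Working it through.** The document gives no figure for HOMA-IR: no effect size, no affected share and no power. There is nothing to reproduce, so the check consists of a comparison of the texts, a calendar count and two small calculations.

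**1. Texts side by side**

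| Item | Glucose tolerance section | Table 2 and footnotes |
|---|---|---|
| Fasting | Stated flatly | Row says fasting; footnote 3 only where possible; glucose row not labelled fasting |
| Glucose specimen | Capillary, local; formula names plasma | Point-of-care reading; no central glucose assay named |
| Day of second insulin | Day 5 | Day 5, or previous or next working day |
| Day of second glucose | Day 5 | Day 5 only |
| Baseline window | Both samples: day of inclusion or day before | Glucose: within 1 day of first dose; central sample: visit 1, day −6 to 1 |

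The two baseline limits are also tied to different events, inclusion and first dose. These can fall on the same day but need not.

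**2. Where a moved sample lands.** Day 5 is four days after day 1, so it falls on a Saturday after a Tuesday start and on a Sunday after a Wednesday start.

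- Saturday visit 6: the last working day is day 4, the next is day 7.
- Sunday visit 6: the last working day is day 3, the next is day 6.

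Glucose is scheduled daily on days 1–5 and next at visit 7 (days 10–13). Samples moved back to day 3 or 4 therefore have a same-day glucose. Samples moved forward to day 6 or 7 have none scheduled.

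**3. How many patients could be affected.** Assumptions: starts are spread evenly over the permitted weekdays and holidays are ignored. Planned N is 312 (Sample size section).

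| Permitted start days | Visit 6 on a weekend | Saturday visit 6 only |
|---|---|---|
| Any day | 2/7 = 28.6% (about 89) | 1/7 = 14.3% (about 45) |
| Monday–Saturday | 2/6 = 33.3% (104) | 1/6 = 16.7% (52) |
| Monday–Friday | 2/5 = 40% (about 125) | 1/5 = 20% (about 62) |

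These are ceilings, because the move is optional and may go backward. The share with no same-day glucose is 0% if no sample moves forward, 14–20% if half of the weekend samples do, and 29–40% if all do.

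**4. Why day 7 is the case that can differ by arm.** The sample is drawn before that day's medication. By the morning of day 7, high-dose patients took oral placebo on day 6, while controls took a tapering dose. On the morning of day 6 the last dose in every arm was the day-5 dose, so this contrast has not yet arisen.

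**5. Effect of a non-fasting sample (values assumed for illustration).** Fasting: 90 × 8 / 405 = 1.78. Non-fasting: 130 × 40 / 405 = 12.84. The ratio is 12.84 / 1.78 = 7.2. This shows how the two errors multiply. It says nothing about how often that happens.

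**6. Effect of capillary versus plasma scale (values assumed).** Take one arm at 110 × 20 / 405 = 5.43 and another at 100 × 15 / 405 = 3.70. The ratio is 1.467 and the difference 1.73. Divide both by a common factor of 1.15: the ratio stays at 1.467 and the difference falls to 1.50. A common factor rescales the index but cancels in an arm ratio, and so also in an analysis of log values.

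**The case against.** Several objections carry weight.

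- **Level of detail.** The article condenses a fuller German protocol, and the SAP was still being finalised. Pairing rules, log transformation and handling of non-fasting samples normally belong there. This stands: their absence is not the point. The point is that one document gives conflicting instructions on fasting and sampling day, and that its weekend rule, followed as written, pairs values from different days.
- **Low stakes.** The endpoint is secondary and its tests are declared descriptive. No confirmatory conclusion depends on it, and the daily point-of-care glucose is unaffected. This stands and limits the severity.
- **Noise, not bias.** Under blinded randomisation, non-fasting samples and meter calibration should add mainly noise. This stands for those two sources. It does not cover the day-7 sample.
- **Specimen.** The document does not say whether the meters report plasma-equivalent values, and a common factor cancels on the log scale. The specimen mismatch is therefore the weakest part.
- **Baseline.** The Glucose tolerance section does give insulin a baseline window. What remains is an inconsistency with Table 2, not a missing window.

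A reader might go further and infer that the glucose-tolerance endpoint is invalid for a sizeable share of patients, or that the error exceeds the effect sought. The documents support neither inference. They give no share of non-fasting or moved samples, the weekend figures are ceilings under assumed start days, and no HOMA-IR effect is stated against which an error could be judged.

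**Conclusion.** The point holds as a contradiction that needs resolving before analysis. The Glucose tolerance section, Table 2 and footnotes 3 and c do not agree on fasting state, specimen or timing. The visit 6 weekend rule leaves any insulin sample moved to day 6 or 7 without a scheduled same-day glucose.

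The unpaired share lies somewhere between 0% and a ceiling of 29–40%. Within it, the day-7 case, where the error can differ by arm, is at most 14–20%. Both figures rest on evenly spread start days and ignore holidays. The non-fasting share cannot be derived from the documents. The consequence is confined to a secondary, descriptive safety endpoint. It warrants a change to the SAP and does not call the trial's main conclusions into question.

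**What to change.** According to the Trial status section, the SAP was being finalised during blind review, so these rules can still be set before unblinding:

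1. Reconcile the Glucose tolerance section with Table 2 and footnotes 3 and c, including the baseline window for the central sample. State the scale on which the local meters report glucose.
2. Compute HOMA-IR only from glucose and insulin taken on the same day. Pair an insulin sample moved back to day 3 or 4 with that day's point-of-care glucose. For a sample moved to day 6 or later, set HOMA-IR to missing in the main analysis.
3. Where fasting status was recorded, restrict the main analysis to fasting pairs, and add a sensitivity analysis on all pairs.
4. Analyse log HOMA-IR at visit 6 adjusted for log baseline, so that a common calibration factor cancels.
5. Do not exclude patients because insulin was started after randomisation. That start may itself be an effect of treatment, and excluding on it could bias the safety comparison. At most, handle patients already on insulin at baseline in a sensitivity analysis.

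The cost is SAP wording plus a blinded check of sampling dates and of whatever fasting information exists. Follow-up has ended, so nothing that was not recorded can be recovered, and the documents do not show that fasting status was captured. The downside is that fewer patients contribute to HOMA-IR.

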### Plans to promote participant retention and complete follow-up {18b}

Sites are trained on patient retention and the importance of completing follow-up. In addition to handing out patient diaries with scheduled visits, study sites are advised to remind patients of follow-up visits actively. In the case of premature termination of study treatment, the patient is asked for agreement with further surveys and the conducting of the follow-up visit. In the case of active withdrawal of consent (i.e., also for follow-up and documentation), the patient’s study participation is terminated, the conducting of further follow-up visits is no longer possible. The reasons for withdrawal of consent (if known) will be documented. The decision to withdraw consent from the study treatment must be without any disadvantage for the patient. Further treatment and follow-up outside the trial should be ensured. Potential loss of follow-up or non-compliance is considered in the statistical analysis plan.

### Data management {19}

Data are recorded directly at the trial sites by the study team in paper-based data collection (case report) forms (CRF) and forwarded to the data management of the Coordination Centre for Clinical Trials (KKS) Halle. In the KKS Halle, the data are continuously recorded and stored in the digital trial database. At an early stage, the accuracy of the data is checked by means of range, plausibility, and consistency checks, with implausible or missing data being corrected or added following requests/queries. The study management software secuTrial® (version 5.5.0.12; interActive Systems GmbH, Berlin, Germany) is used for data entry and query management—a validated, good clinical practice (GCP)-compliant database-supported complete solution for conducting clinical studies. All changes made to the data are stored in an audit trail. The study software has a study-specific adaptable user and role concept. The database is integrated into a general information technology (IT) infrastructure and security concept with a firewall and backup system. The data are backed up daily. The database will be closed once the input and the quality checks including blind review by the biometrician have been completed. The data are then forwarded for final evaluation to the responsible biometrician.

### Confidentiality {27}

Information about trial patients is kept confidential and managed under the applicable data protection laws and regulations. Access to the data is strictly limited to authorized persons.

The investigator and sponsor must ensure data protection of the patients. Patients must not be identified by names in any documents submitted to the sponsor. It will be ensured that all study materials and data are appropriately pseudonymized in accordance with data protection regulations prior to scientific use. Patients are informed that their study-related data will be stored in pseudonymized form. All data remain confidential and are subject to medical confidentiality. According to the national GCP regulation, these documents must and will be kept for at least 10 years.

### Plans for collection, laboratory evaluation, and storage of biological specimens for genetic or molecular analysis in this trial/future use {33}

n/a: The trial does not involve genetic or molecular analysis of biological specimens. No specimens will be stored for future use.

## Statistical methods

### Statistical methods for primary and secondary outcomes {20a}

The primary confirmatory analyses will be based on the intention-to-treat population (ITT), which will include all randomized patients. The analysis will be done according to the intention-to-treat principle; this means every patient remains in the treatment group as allocated by randomization. The per-protocol population (PP) will be formed from the ITT. Only patients with major protocol violations will be excluded. The details will be described in the final statistical analysis plan.

The PP will be the secondary analysis population for PP analysis to confirm the results of the ITT analysis.

The confirmatory analysis of the primary endpoint is planned after complete documentation and data cleaning including visit 9. The confirmatory analysis aims on showing the superiority of one or both of the high-dose treatments in comparison with the standard therapy. Therefore, two analyses of covariance (adjusted for baseline PTA) will be performed at a local significance level of α = 0.025 (two sided), which means for a global significance level of α = 0.05 (two sided) for the statistical evaluation of the primary endpoint.

The differences in the primary endpoint between the high-dose groups and the standard group will be estimated with 97.5% confidence intervals (being confirmatory and consistent to the test procedure) and with 95% confidence intervals (being comparable to results usually presented in the literature).

The sample size of the study was planned to achieve a high power for the comparisons of high dose vs. standard dose. But, if superiority of both high-dose treatments versus the standard treatment can be shown, both high-dose treatment arms will be compared at a significance level of α = 0.05 (two sided) and the difference will be estimated with 95% confidence interval as a secondary objective.

The data of the ITT and PP will be statistically described in detail. This includes:Listings of all documented data for every patient.Summary tables of all variables. Discrete variables will be described by absolute and relative frequencies. Continuous variables will be described by statistical characteristics (minimum, maximum, quartiles, median, mean, standard deviation).

The secondary endpoints will be analyzed as follows:Speech discrimination using Mann–Whitney tests as these values are usually not normally distributed.Comparison of patients with complete, partial, or no improvement will be compared with a Cochrane–Armitage test for trend.Data from QoL questionnaires using chi-squared tests and Mann–Whitney tests as adequate.

All statistical tests in connection to the secondary endpoints will be performed for descriptive purposes. The *p *values will be given without adjustment for multiple testing.

To evaluate the role of the baseline PTA as a prognostic or predictive factor for the primary and secondary endpoints, it is planned to analyze two subgroups according to baseline hearing loss (< 81 dB vs. ≥ 81 dB). The analysis will be the same as that for the primary intention-to-treat analysis including a test for interaction of baseline hearing loss and therapy.

Safety analyses will be performed in the safety population including all patients for whom one of the randomized treatments was started. Here, patients will be analyzed according to treatment received. Rates of adverse events and of serious adverse events will be calculated.

All confirmatory analyses were fully specified in the trial protocol. Other details of the statistical analysis will be fixed at the latest in the Statistical Analysis Plan, to be prepared during blind review before database lock.

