### Sample size {14}

This three-armed trial (randomization ratio: 1:1:1) is aimed at comparing standard-dose systemic therapy with two types of high doses of systemic therapy concerning the primary endpoint using two individual statistical tests assuming a normal distribution of the primary endpoint in the population. For a global significance level of 0.05, we adjust for two tests using a local level for each test of 0.025. The following assumptions are based on the available literature [32]. A sample size of 88 in each group will have 80% power to detect a difference between high dose and standard dose, when the true difference in means is −10.0 (e.g., the difference between a group 1 mean, μ1, of 30.7 and a group 2 mean, μ2, of 40.7) assuming that the common standard deviation is 21.3. The sample size calculation was performed for two-sample *t* tests with nQuery Version 7.0. Assuming a dropout rate of approximately 15%, a total of 312 patients need to be randomized (1:1:1) to maintain at least 264 evaluable patients with complete data (high-dose dexamethasone: 104; high-dose prednisolone: 104, standard prednisolone: 104).

Systemic glucocorticoids are the standard treatment in ISSHL. Since the study drugs thus do not involve a completely new therapeutic concept, patient compliance is generally estimated as high. We assume a rate of loss to follow-up of 15%. This estimate is based on two recent RCTs on ISSHL. Nosrati-Zarenoe and Hultrantz (2012) randomized 103 patients and were able to analyze 88 (85%) on day 8 of the assessment and 73 (71%) at the 3‑month time point [26]. In the study of Rauch et al. (2011), 221 of 255 patients (87%) completed the intervention and 2‑month follow-up (per-protocol analysis [32]).

The trial will be analyzed according to the intention-to-treat principle including all randomized patients. A per-protocol analysis will be performed as sensitivity analysis.

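### Testing each high-dose arm at a fixed 0.025 is valid but less powerful than a Holm step-down at the same 5% familywise error, mainly for showing both arms superior

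*Protocol article*

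**What the plan says.** The section Sample size {14} of the protocol article plans the comparisons "using two individual statistical tests assuming a normal distribution of the primary endpoint in the population" and sets the level: "For a global significance level of 0.05, we adjust for two tests using a local level for each test of 0.025". It continues: "A sample size of 88 in each group will have 80% power to detect a difference between high dose and standard dose", for a difference of 10 dB and a common SD of 21.3. No power is given for showing both arms superior.

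The section Statistical methods for primary and secondary outcomes {20a} repeats the rule for the analysis: "two analyses of covariance (adjusted for baseline PTA) will be performed at a local significance level" of 0.025, two-sided. The stated aim is superiority of one or both high-dose arms. The same section ties 97.5% confidence intervals to the test and describes them as consistent with it. It opens a comparison of the two high-dose arms at 0.05, as a secondary objective, "if superiority of both high-dose treatments versus the standard treatment can be shown". It also says that the confirmatory analyses are completely specified in the protocol and leaves only other details to the SAP. No step-down between the two primary tests is described.

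**The concern.** Each high-dose arm has to reach 0.025 whatever the other arm shows. Once one null hypothesis has been rejected at 0.025, the Holm procedure allows the other to be tested at 0.05 with the familywise error still at most 0.05. Holm rejects everything the fixed split rejects, and sometimes more. The plan already passes the full 0.05 on to the third comparison after two rejections, but passes nothing on between the first two.

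At stake is power for the second arm. The result in which both arms are superior is part of the stated aim and is the only way to the comparison of intravenous prednisolone with oral dexamethasone. Recruitment has ended, so this power can no longer be raised by enrolling patients.

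**Working it through.** **Inputs, all from Sample size {14} and Statistical methods {20a}.** Difference 10 dB; common SD 21.3; 88 evaluable per arm, allocated 1:1:1; two-sided local level 0.025; dropout 15%. The article gives no correlation between baseline and outcome, so no gain from the covariate is included, as in the plan's own calculation.

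**1. The plan's figure.** Normal approximation: n = 2 × (SD/δ)² × (z₀.₉₈₇₅ + z₀.₈₀)² = 2 × (21.3/10)² × (2.241 + 0.842)² = 86.2, so 87 per arm. With the noncentral t distribution, power is 79.7% at 87 and 80.2% at 88. Dropout: 88/0.85 = 103.5, so 104 per arm and 3 × 104 = 312. The stated 88, 264 and 312 reproduce.

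**2. The two rules.** The standard error of a difference is 21.3 × √(2/88) = 3.21 dB. With 174 degrees of freedom the critical values are 2.261 (level 0.025) and 1.974 (level 0.05).
- Planned rule: reject each hypothesis if its |t| exceeds 2.261.
- Holm: reject the larger |t| if it exceeds 2.261; if so, reject the other if it exceeds 1.974.

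**3. Simulation.** Three normal arms with a shared control, two separate two-arm t-tests, 1,000,000 trials per scenario.

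| Per arm, true differences | At least one, both rules | Both superior, planned | Both superior, Holm |
|---|---|---|---|
| 88, 10 and 10 dB | 91.5% | 69.1% | 78.3% |
| 104, 10 and 10 dB | 95.3% | 78.6% | 86.0% |
| 88, 7.5 and 7.5 dB | 69.7% | 36.4% | 47.2% |
| 88, 10 and 5 dB | 81.4% | 23.2% | 32.5% |

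The last two rows use assumed effects, not the plan's, to show the range.

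**4. Per-comparison power at 10 dB, 88 per arm.** Planned 80.3%, Holm 84.9%. Check: by symmetry each arm receives half of the extra joint rejections, 80.3% + (78.3% − 69.1%)/2 = 84.9%.

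**5. Error control.** With no true difference in either arm, the probability of any rejection is 4.7% under both rules. If one arm has a true 10 dB effect and the other none, the ineffective arm is rejected in 2.5% of trials as planned and 4.3% with Holm. That is higher, but within the 5% limit.

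**6. Sample-size equivalent.** The fixed split needs about 104 evaluable per arm (78.6%) to match Holm at 88, that is 3 × 16 = 48 more evaluable patients.

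**7. Intervals.** Holm and the planned rule differ only when the second arm's |t| lies between the two critical values, and then that arm's 97.5% interval includes zero. At 10 dB and 88 per arm this happens in 78.3% − 69.1% = 9.2% of trials.

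**8. Refinements.** One three-arm model with pooled variance adds about 0.2 points to both-superior power under Holm (78.3% to 78.5%). Step-down Dunnett on that model gives 78.7%, and 92.0% for at least one success.

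**The case against.** The strongest reply is that nothing here is wrong. The two sections agree, the sample size reproduces, and a fixed Bonferroni split is a standard, valid choice. All of this stands; the point concerns efficiency only.

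Second, the fixed split has a benefit that the plan names: the 97.5% intervals always agree with the test. Holm gives this up in the second-step cases. This also stands, so a reader should not infer that the gain is free. It costs no patients and keeps the 5% familywise limit, but it has a reporting cost.

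Third, the plan powers each single comparison, and that target is met. The probability of at least one success does not change, and the gated comparison is only a secondary objective. A reader might infer that the trial is underpowered for its main aim; the document does not support this. The gain falls on the second arm and on the gate.

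Fourth, a reader might infer that two separate analyses waste a third of the data. The article does not say word for word that each analysis uses only two arms, though this is the natural reading. Even on that reading, pooling changes little and adds the assumption of a common baseline slope.

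Fifth, this is more than SAP wording. The article places confirmatory analyses in the protocol, data collection is complete, and under Who will be blinded {17a} the SAP authors see all final data except the allocation. A more liberal rule adopted now needs a documented reason. That bears on how the change is made; it does not remove the gain.

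**Conclusion.** The point holds as a worthwhile improvement to a valid procedure. Under the plan's own assumptions, Holm adds about 9 points to the probability of showing both arms superior with 88 per arm, and about 7 points (79% to 86%) if all 104 per arm are analysed. It adds nothing to the probability of at least one success.

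These figures assume normal outcomes, equal SD of 21.3, a true 10 dB effect in both arms and no gain from baseline adjustment. Adjustment would raise all the power figures and narrow the gap, by an amount that cannot be computed from the article. With the smaller assumed effects the gain is 9 to 11 points. Nearly all of it comes from the step to 0.05; the choice of model is secondary.

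**What to change.** - On the two planned analyses of covariance, test the smaller p-value at two-sided 0.025. If it is significant, test the other at 0.05. Keep the comparison of the two high-dose arms at 0.05 after both rejections.
- Record this before unblinding as a change to the protocol-specified confirmatory rule, with its justification, and carry it into the SAP. The Trial status section places the trial in blind review with the SAP still being finalized, so this was possible when the article was written. After unblinding, the change would look data-driven.
- Reword the statement that the 97.5% intervals are consistent with the test, for example by presenting them as simultaneous intervals. Explain that an arm rejected only at the second step has a 97.5% interval that includes zero.
- A single three-arm model or step-down Dunnett is optional and adds under one point.

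The change needs no patients and no new data. Its costs are the documented departure from the protocol and the looser link between test and interval.
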